### **.33.3 Research methods and steps**

As this is a randomized controlled study, the physician will decide on the treatment plan according to the instructions and the clinical pathway. The investigator will review the patient's medical history and test report and determine patient eligibility based on the inclusion and exclusion criteria. Patients must sign the latest IRB / IEC approved informed consent (I C F) before performing data collection. In this non-intervention study, the investigators collected clinical assessment data at baseline and after the intervention (2 weeks).

(1) Informed consent and enrollment

Subjects who provided informed consent and met all other inclusion / exclusion criteria were considered as enrolled in the study.

(2) Subject identification number

The numbers were grouped by random number table, and each subject was given a unique identification number (one researcher selected the second column in the third row according to the random number table, all numbers divided by 2, odd to the control group and even to the observation group). This identification number will be used for all study documents (such as a language assessment form, etc.). Furthermore, according to the data privacy regulations, unique identification numbers are allowed as long as it does not contain combined information that identifies the subject.

(3) Research process:

The observation group is receiving routine treatment (including medication, routine care in neurology department, and speech rehabilitation)

Teaching guidance, etc.) on the basis of computer assisted aphasia idiom reading training, the specific method for the use of computer software Powerpoint2003, computer screen in turn white background black idioms (idioms from the student practical idiom dictionary), a total of 50, the computer screen will display idioms, idioms in the form of words, idioms are equipped with auxiliary reading prompt material, including the corresponding idioms unsealed or expanded into the form of characters, words, sentences, paragraphs. At the bottom of the screen, there are the button of each prompt and the button to switch the next idiom. First, the speech rehabilitation teacher asks the patient to read the idiom. When the patient cannot read the idiom, click the corresponding prompt button (voice, video or picture prompt) to help the patient read. The training period is 2 weeks, per day for 40 minutes, the training ground is a clinical classroom.

The control group only underwent conventional treatment, including medication, routine care in neurology department, education and guidance of speech rehabilitation, but not regular speech rehabilitation training. Before and after the study, the Chinese aphasia examination method was used (ABC) to evaluate its language function.

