### **3.4 Data management**

Subject data should be reported quickly, completely and correctly, and all steps related to data management should be recorded to check data quality and test implementation. To ensure the confidentiality of the database, it should have the maintenance and support procedures of the computer database. Design the clinical report form and the corresponding computer program that can be read and input by the computer. Subject assignment must be performed according to the randomized protocol determined by the trial design, and sealed codes for each study subject should be kept by the investigator.

System of original data records: 1) Before the start of the study, the project leader should discuss with the researchers and supervisors how to record the information about the clinical research in the original data and establish the requirements for the original records. 2) The format of the clinical research information record provided by the project leader in the original data (CRF table). 3) The original data is signed and dated by the completed researcher according to the industry practice of the medical documents. 4) The name of the study subject and the study number should be placed on each page of the data. 5) All corrections to the original data shall be made by

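### The subject ID, read plainly, carries the arm onto the language assessment form, and the investigator who judges eligibility keeps the sealed codes, so allocation concealment and masked scoring are not adequately protected

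*Protocol*

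**What the plan says.** Protocol section .33.3 (Research methods and steps), item (2), deals with numbering and allocation together:

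- Issue of the number: "The numbers were grouped by random number table, and each subject was given a unique identification number".
- Start of the sequence, in the bracket attached to that sentence: "one researcher selected the second column in the third row according to the random number table".
- Allocation rule, in the same bracket: "all numbers divided by 2, odd to the control group and even to the observation group".
- Use of the number, in the next sentence: "This identification number will be used for all study documents (such as a language assessment form, etc".

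Three further statements bear on who knows what:

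- Eligibility: section .33.3 has the investigator "determine patient eligibility based on the inclusion and exclusion criteria".
- Outcome data: the same section says "the investigators collected clinical assessment data at baseline and after the intervention (2 weeks".
- Custody: section 3.4 (Data management) says "sealed codes for each study subject should be kept by the investigator". It also requires assignment to follow the randomisation scheme, and the study number to appear on each page of the data.

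Section .33.3 gives the training to the observation group only; controls have conventional treatment without regular speech training. The text shown names no masked assessor, no list holder separate from recruitment, and no second subject number independent of the random number.

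**The concern.** Two safeguards are at issue.

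**Scoring.** Patients and therapists cannot be masked when only one arm is trained, so masking the assessor is the main protection left for the ABC and for the daily-communication scale (CADL). An ID whose parity gives the arm, on the form where the score is entered, would defeat it. An assessor who expects training to help may then score the trained arm more generously. The between-group t-test in section 3.5.1 cannot separate such a shift from a treatment effect.

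**Enrolment.** If the person who judges eligibility also holds the assignments, the next allocation could become known before a patient is accepted. Patients with better prospects could then be steered to one arm. Analysis cannot reliably remove either bias afterwards.

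**Working it through.** The protocol states no figure to reproduce on this point. As shown, it gives no sample size, SD, effect size or expected rates. The check is mainly a reading of the text.

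**Step 1. Does the ID carry the arm?** The item is headed as the subject identification number. One sentence groups the numbers by the random table, gives each subject a unique number, and states the parity rule in brackets. The next sentence sends this number to all study documents and gives a language assessment form as its example. No other number is described. There are two readings:

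- The ID is the table number. Parity then identifies the arm with probability 1 for anyone who knows the rule.
- The ID is a separate number, and the rule applies only to table entries. The ID then says nothing about the arm, and a guess is right with probability 0.5 under 1:1 allocation.

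The sentence structure favours the first reading but does not settle it.

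**Step 2. Is scoring protected on the second reading?** Investigators collect the assessments at baseline and 2 weeks, and the investigator keeps the codes. No masked assessor is named, and the care given differs visibly between arms. Masking is not secured on either reading.

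**Step 3. Is enrolment protected?** The eligibility decision and custody of the codes sit with the same role. The codes are sealed, which is the only concealment measure stated. The text names no one outside recruitment who holds or releases them.

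**Step 4. What could a scoring shift do? (illustration only)**

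- From the protocol: significance level 0.05 (section 3.5.1). Sidedness is not stated; two-sided is assumed.
- Assumed: *n* per arm of 20, 30 or 50; no true effect; unmasked scoring that moves one arm by *b* = 0.1, 0.2 or 0.3 SD.

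By the normal approximation,

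P(reject) = Φ(δ − 1.96) + Φ(−δ − 1.96), with δ = b / √(2/n).

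For *n* = 30 and *b* = 0.2: δ = 0.2 / √(2/30) = 0.775, so P = Φ(−1.185) + Φ(−2.735) = 0.118 + 0.003 = 0.121.

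| n per arm | b = 0 | b = 0.1 | b = 0.2 | b = 0.3 |
|---|---|---|---|---|
| 20 | 5.0% | 6.2% | 9.7% | 15.8% |
| 30 | 5.0% | 6.7% | 12.1% | 21.3% |
| 50 | 5.0% | 7.9% | 17.0% | 32.3% |

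A fixed shift does more harm in a larger trial, because extra patients reduce random error but leave the bias unchanged.

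**The case against.** The strongest reply is that the text does not prove the defect.

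- **The ID.** A reader might infer as established fact that the ID's last digit is the arm. The documents do not support that certainty. The sentence could mean that subjects' numbers were sorted into groups with the help of the table, and table entries can repeat, which fits poorly with unique IDs. This stands as a limit on the claim. It does not remove the need to clarify the rule, and Step 2 does not depend on it.
- **Rebuilding the sequence.** A reader might infer that anyone could reconstruct the allocation from the stated start cell. The protocol identifies neither the table nor the reading direction, so it cannot be done from the protocol alone.
- **Enrolment.** A reader might infer that there is no concealment at all. The codes are sealed, and the researcher who used the table is not said to be the one who judges eligibility. The supportable statement is that concealment is not adequately protected, because the sealed codes stay with the role that decides eligibility.
- **Scoring method.** The protocol does not describe how either scale is scored. That a rater's judgement enters the score is an assumption.
- **The figures.** They would apply to any unmasked trial with the same inputs and do not isolate what the ID adds. This is correct.
- **Renumbering alone.** A neutral ID would not mask investigators who hold the codes and collect the scores. Section .33.3 also draws data from routine treatment records, where the care given may be visible. This stands too, and the fix has to go beyond the number.

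**Conclusion.** The point holds in a limited form. On its plain reading, section .33.3 lets the assessment form reveal the arm. On any reading, sections .33.3 and 3.4 together leave eligibility, code custody and outcome collection with the investigator role, without a stated separation. Allocation concealment and masked scoring are therefore not adequately protected. These are matters of trial conduct that the protocol itself fixes, so an analysis plan would not normally settle them.

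The documents do not show that any score or enrolment was biased, and they give no basis for a trial-specific size. Across the assumed grid of 20 to 50 per arm and shifts of 0.1 to 0.3 SD, the false-positive rate runs from about 6% to 32% against a nominal 5%. It is illustrative only, and the conclusion does not rest on it.

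**What to change.** 1. **Section .33.3, item (2):** give each subject a sequential enrolment ID unrelated to the random number. Use only that ID on the ABC and CADL forms and the eCRF, and keep the random number and arm on a separate list.
2. **Sections .33.3 and 3.4:** have the list and sealed codes held by an existing team member who does not recruit, score or enter outcome data. Release each assignment only after consent, eligibility and baseline ABC and CADL scores are recorded. The staff who receive the case report forms for double entry are not suitable holders, because they handle the outcome data.
3. **Section .33.3:** where existing staffing allows, have the 2-week ABC and CADL scored by a current team member who neither delivers the training nor has access to the list. Without this step, a neutral ID closes only one of the routes by which the scorer can learn the arm.

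The cost is a new numbering rule and a minor reassignment of roles within the team. No extra patients, visits or measurements are needed. In a small team the third step may be the hardest to staff.

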#### (4) Data source / data collection process

Data from this study were obtained by extracting the routine clinical treatment records of the enrolled subjects. The investigator is required to fill in the study's e-case report form (eCRF) and or records based on the information entered in the patient medical records during the entire monitoring period.

(5) Data collection steps: (fill in by yourself according to the research content)

**Baseline period:** General information table and score of Aphasia Battery Of Chinese (ABC) scale and Comprehensive activities of daily living (CADL) scale

---

Routine diagnosis and treatment period: score of Aphasia Battery Of Chinese ( ABC ) scale and Comprehensive activities of daily living(CADL) scale

### **3.4 Data management**

Subject data should be reported quickly, completely and correctly, and all steps related to data management should be recorded to check data quality and test implementation. To ensure the confidentiality of the database, it should have the maintenance and support procedures of the computer database. Design the clinical report form and the corresponding computer program that can be read and input by the computer. Subject assignment must be performed according to the randomized protocol determined by the trial design, and sealed codes for each study subject should be kept by the investigator.

System of original data records: 1) Before the start of the study, the project leader should discuss with the researchers and supervisors how to record the information about the clinical research in the original data and establish the requirements for the original records. 2) The format of the clinical research information record provided by the project leader in the original data (CRF table). 3) The original data is signed and dated by the completed researcher according to the industry practice of the medical documents. 4) The name of the study subject and the study number should be placed on each page of the data. 5) All corrections to the original data shall be made by

Correct investigator is signed and dated.6) All the information and data recorded on the case report form shall be recorded in the original data.7) Completion and handover of the case report form: CRF filling is made by the patient to find the corresponding entry serial number according to the patient case number and enter the CRF form. After the filling, the researchers will review the patients.8) The project informed consent was kept in each electronic CRF form after the patient.9) Fill in the completed case report form, after the intervention and early follow-up will be sent to the clinical trial data management personnel unified database and the project entry personnel double entry, kept by the researchers lock and save electronic original data, late follow-up data after the project designated entry personnel double entry.10) Data entry and modification: the relevant medical record information entered in each stage will be locked by the signature of the patient and the signature of the supervisor. All data will be entered by computer software. During this period, the questionable CRF form is forwarded to the investigator through the clinical supervisor for data review, and the investigator should answer and return as soon as possible.11) Data locking: the locked data file is not allowed to be changed again. The database will be submitted to the statistical analysts for statistical analysis as required in the statistical plan.

### **3.5 Statistical analysis**

#### **3.5.1 Statistical Methods**

Statistical analysis was performed using the statistical software SPSS20.0, Data are represented in terms of ( $\bar{x} \pm s$ ), The study language function score and patient general data (age and disease duration) are the measurement data, Therefore, the t-test of two independent samples was used to compare between the experimental and

control groups, Two respective internal pre-posterior scores were compared using a paired sample t-test, Meverage of language function difference before and after the study using paired sample t-test; patient general data (including sex and stroke type) are count data, The chi-square test was used, Significance level =0.05.

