**Baseline data**

Gender, age, education, type of stroke, area of disease, cerebral infarction, Aphasia Battery Of Chinese (ABC) score, Comprehensive activities of daily living (CADL) scale score

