### **statistical analysis technique**

Two independent sample t-test, paired sample t-test

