### **.3.13 Subjects**

The subject population in this study was patients with non-fluent aphasia after stroke.

Selection criteria:

- (1) Was diagnosed with aphasia through the aphasia Screening Form of China Rehabilitation Research Center, and was a non-fluent aphasia patient;
- (2) Primary school education or above;
- (3) Clear awareness and cooperation, normal intelligence before the onset, and no history of mental illness;
- (4) It is non-fluent aphasia after ischemic stroke, and the cerebral infarction site is the posterior inferior frontal gyrus of the dominant side, and the disease

---

In the stable period, you can adhere to sit alone for more than 30min;

(5) Informed and agreed to participate in this test, and sign the informed consent form;

(6) Age is from 45 to 70 years old

Exclusion criteria: (means the object that does not meet the study requirements even if they meet the inclusion criteria)

(1) Cognitive impairment;

(2) Mental disorders;

(3) Binocular corrected visual acuity <1.0 or visual field defect;

(4) Hearing impairment;

(5) Disarthria; loss of speech;

(6) Complete aphasia, Wernicke aphasia, transcortex sensory aphasia and transcortex mixed aphasia;

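### The between-arm comparison of the language score is an unadjusted two-sample t-test, although the same score is measured at baseline; baseline-adjusted ANCOVA would gain precision and correct chance imbalance with no new data

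*Protocol*

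**What the plan says.** Section 3.5.1 classes the outcome and two patient characteristics together: "The study language function score and patient general data (age and disease duration) are the measurement data". It then gives the between-arm test: "Therefore, the t-test of two independent samples was used to compare between the experimental and" control groups. Two further clauses follow. One covers change within each arm: "Two respective internal pre-posterior scores were compared using a paired sample t-test". The other is poorly translated, but it also names a paired test: "language function difference before and after the study using paired sample t-test". The significance level is 0.05.

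The analysis line in the protocol summary matches this and names no adjusted model: "Two independent sample t-test, paired sample t-test".

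Baseline scores are available. The baseline data list in the summary begins "Gender, age, education, type of stroke, area of disease, cerebral infarction, Aphasia Battery Of Chinese (ABC) score" and goes on to the CADL score. The data collection steps under Research methods and steps give the baseline period as "General information table and score of Aphasia Battery Of Chinese (ABC) scale" together with CADL. Both scales are scored again later, and the same section places the post-intervention assessment at 2 weeks. Allocation is by odd and even numbers from a random number table, with no blocking or stratification by severity described.

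**The concern.** When the same scale is measured before and after treatment, part of the spread in the final score is spread that was already there at baseline. A t-test on the final score counts that part as noise. It also passes a chance difference in starting severity into the estimated effect, in proportion to rho. Nothing in the described allocation limits such a difference. The paired tests do use the baseline score, but each looks at one arm alone. Finding a significant change in one arm and not in the other does not test the difference between arms.

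At stake are the width of the confidence interval for the treatment effect and how far the result can be trusted if the arms happen to start unequal.

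**Working it through.** **Inputs from the protocol.** Two-sample t-test between arms; significance level 0.05; one baseline and one 2-week assessment; two arms, 1:1 in expectation. The protocol gives no sample size, SD, expected difference, power or rho, so there is no figure of its own to reproduce.

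**Assumptions.** Two-sided test; equal SD at both times; linear relation between the scores; rho from 0.3 to 0.8. For the power illustration only: 30 per arm and a true difference of 0.5 SD.

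**Step 1: relative variance.** With the variance of the 2-week score set to 1, the variance that matters for the between-arm difference is:

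- t-test on the 2-week score: 1
- t-test on change: 2(1 − rho)
- ANCOVA: 1 − rho²

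The loss in effective sample size against ANCOVA is therefore 1 − (1 − rho²) = rho² for the 2-week score. For change it is 1 − (1 − rho²)/[2(1 − rho)] = 1 − (1 + rho)/2 = (1 − rho)/2.

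| rho | Loss, 2-week score (rho²) | Loss, change ((1 − rho)/2) | ANCOVA SE as a fraction of the 2-week-score SE (√(1 − rho²)) |
|---|---|---|---|
| 0.3 | 9% | 35% | 0.95 |
| 0.5 | 25% | 25% | 0.87 |
| 0.6 | 36% | 20% | 0.80 |
| 0.8 | 64% | 10% | 0.60 |

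The loss with change scores is the smaller of the two only when rho exceeds 0.5. They are equal at 0.5, and below that change scores lose more.

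**Step 2: power under the assumed 30 per arm and 0.5 SD** (noncentral t, with the standardised difference 0.5 divided by the square root of the relative variance).

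| rho | 2-week score | Change | ANCOVA |
|---|---|---|---|
| 0.3 | 48% | 36% | 51% |
| 0.5 | 48% | 48% | 59% |
| 0.6 | 48% | 57% | 66% |
| 0.8 | 48% | 85% | 89% |

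**Step 3: chance imbalance.** At 30 per arm the baseline mean difference has standard error √(2/30) = 0.258 SD. A difference above 0.3 SD in either direction is 0.3/0.258 = 1.16 standard errors, which has probability about 25%. An imbalance of 0.3 SD shifts the unadjusted estimate by rho × 0.3: 0.09 SD at rho 0.3, 0.15 at 0.5, 0.18 at 0.6 and 0.24 at 0.8.

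With no treatment effect and a baseline difference of z standard errors, the unadjusted test statistic is approximately normal with mean rho × z and variance 1 − rho². At z = 1.96 the chance of a result beyond ±1.96 is about 8% at rho 0.3, 13% at 0.5 and 26% at 0.8. Averaged over all randomisations it is 5%.

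**The case against.** **The before-after clause may be a mistranslated comparison of change between arms.** Within-arm change has just been covered, so the clause is otherwise redundant. If that was meant, baseline is already used and, at a high rho, most of the loss disappears: at rho 0.8 the power is 85% against 89% for ANCOVA. This stands as a caution about size. It does not remove the point, because the clause as written names a paired test, and ANCOVA is at least as efficient as a test of change in large samples over the whole range.

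**A reader might infer that the trial gives up much of its power, or that most of the outcome variance is baseline severity.** The documents do not support either. They give no rho, sample size or effect. At rho 0.3 the power in the illustration moves only from 48% to 51%, and at rho 0.6 baseline explains 36% of the variance. A high rho is plausible for one scale repeated after 2 weeks, but eligibility requires a single infarct site and excludes several aphasia types, which may narrow the range and lower rho. The sample size formulas also rest on the proportion improved, so t-test power is not what the trial was sized on.

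**A reader might infer that the t-test is wrong.** It is not. Under randomisation it is unbiased and holds its level on average.

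**Some neighbouring points look tempting but are not established.**
- Stroke type is to be tested by chi-square although eligibility states "It is non-fluent aphasia after ischemic stroke". It is constant only if the variable means ischaemic against haemorrhagic, which the text does not say.
- Disease duration is missing from the summary's baseline list, but it may be on the general information table, whose fields are not shown.
- Dropping the balance tests would not change any treatment estimate.
- Section 3.5.1 does not name CADL. That it is compared by the same test is an inference from the summary.

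**Conclusion.** The point holds as a matter of precision and of chance imbalance. The only between-arm comparison of the language function score that the protocol states is unadjusted, and the baseline score enters only paired tests that cannot compare the arms. Against ANCOVA, the loss in effective sample size is rho² if the 2-week score is tested: 9% to 64% for rho from 0.3 to 0.8. It is (1 − rho)/2 if change was meant: 35% down to 10% over the same range. Both rest on an assumed rho, equal SDs and a linear relation; the power figures also rest on an assumed 30 per arm and 0.5 SD. The overall type I error is not affected. A separate statistical plan may exist, but the protocol itself names the unadjusted test in two places, so a plan that used ANCOVA would contradict it.

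**What to change.** In section 3.5.1 and in the analysis line of the summary, replace the between-arm t-test on the language scores with an ANCOVA: 2-week score as outcome, with arm and the baseline value of the same score as terms. Apply it to each ABC score that is compared between arms, and to CADL if CADL is compared between arms. Report the adjusted difference with its 95% CI. Keep the paired tests only as descriptive summaries within each arm, and rewrite or delete the unclear clause on the before-after difference.

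The cost is a change of wording. The baseline scores are already collected and the planned software, SPSS 20.0, fits the model. No extra assessment, patient or data field is needed.

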### **Observational indicators**

Aphasia Battery Of Chinese (ABC ) scale,all items score,  
including listening to understanding, oral expression, writing,reading four items; Comprehensive activities of daily living(CADL) scale score,, including 22 daily communication activities

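### The arm comparison is an unadjusted t-test although baseline ABC/CADL scores and education are collected; an ANCOVA on baseline score, with education as a secondary covariate, would be more precise

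*Protocol*

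**What the plan says.** The Protocol's synopsis gives the whole analysis as "Two independent sample t-test, paired sample t-test". Section 3.5.1 expands this. For the measurement data it says "Therefore, the t-test of two independent samples was used to compare between the experimental and" control groups, with paired t-tests for before-and-after scores and chi-square tests for count data. No covariate appears.

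The baseline variables in the synopsis are listed as "Gender, age, education, type of stroke, area of disease, cerebral infarction, Aphasia Battery Of Chinese (ABC) score", followed by the CADL score. Education and the baseline values of both outcome scales are therefore available for every patient.

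Four other statements bear on education:
- Entry requires "Primary school education or above", with no upper limit (section .3.13 Subjects).
- The ABC is scored in four domains, "including listening to understanding, oral expression, writing,reading four items" (Observational indicators).
- The training starts from written idioms: "First, the speech rehabilitation teacher asks the patient to read the idiom" (section .33.3, research process). When the patient cannot read one, voice, video or picture prompts are available.
- Allocation is by odd or even numbers from a random number table, with no stratification (section .33.3).

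In section 3.5.1, "The study language function score and patient general data (age and disease duration) are the measurement data". Sex and stroke type are named as count data, in a list worded as examples. Education appears in neither list.

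**The concern.** Schooling before the stroke plausibly influences reading and writing scores, and the intervention is itself a reading task. Baseline ABC and CADL scores should predict the 2-week scores more strongly still. A plain t-test puts all of that predictable variation into the error term. It also makes no correction if simple allocation happens to give one arm more of the better-schooled or less impaired patients.

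Two things are at stake: precision that could be had from data already collected, and how far the one realised comparison can be trusted if the arms differ by chance. The reading and writing domains are the most exposed. Because section 3.5.1 positively prescribes the unadjusted test, this is a stated choice and not a detail left open for a later plan.

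**Working it through.** **Figures in the plan.** There is none to reproduce. The Protocol defines the two response rates for the sample size but gives no values, and it states no N, power, SD or correlation. Only the 0.05 significance level is given. Everything below is illustrative.

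**Assumed inputs.** r is the correlation of education with the score, taken as 0.2 to 0.5 and equal at baseline and at 2 weeks. ρ is the correlation of baseline with 2-week score, taken as 0.7 to 0.9. Variances are relative to a t-test on the 2-week score (1.00).

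**Step 1: education alone.** Relative variance is 1 − r².

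| r | 1 − r² | Variance removed | Power, 30 per arm, d = 0.65, two-sided 0.05 |
|---|---|---|---|
| 0 (plan as written) | 1.00 | – | 69.7% |
| 0.2 | 0.96 | 4% | 71.5% |
| 0.3 | 0.91 | 9% | 73.7% |
| 0.4 | 0.84 | 16% | 77.1% |
| 0.5 | 0.75 | 25% | 81.6% |

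**Step 2: baseline score alone.** Relative variance is 1 − ρ². At ρ = 0.7 it is 0.51 (51% removed); at ρ = 0.9 it is 0.19 (81% removed).

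**Step 3: education on top of baseline score.** The further share of residual variance removed is the squared partial correlation, r²(1 − ρ)² / [(1 − ρ²)(1 − r²)].
- ρ = 0.7, r = 0.5: 0.25 × 0.09 / (0.51 × 0.75) = 0.0225 / 0.3825 = 5.9%.
- ρ = 0.9, r = 0.2: 0.04 × 0.01 / (0.19 × 0.96) = 0.0004 / 0.1824 = 0.2%.

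Take a comparison that has 69.7% power with baseline score already in the model. Adding education raises it to between 69.8% and 72.3%.

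**Step 4: chance imbalance.** Assume 30% to 50% of patients have primary schooling only. Under simple odd/even allocation the arms differ by 20 percentage points or more in about 18% to 22% of trials at N = 40, and about 10% to 13% at N = 60. With arm sizes forced equal, the figures are 23% to 27% at 20 per arm and 12% to 16% at 30 per arm. If primary-only patients score 0.5 to 1.0 SD lower, a 20-point imbalance shifts an unadjusted difference by 0.20 × 0.5 = 0.1 SD to 0.20 × 1.0 = 0.2 SD. If the same gap exists at baseline, adjusting for baseline score leaves (1 − ρ) of this: 0.1 × 0.1 = 0.01 SD to 0.3 × 0.2 = 0.06 SD.

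**Step 5: validity.** In 20,000 simulated trials of 30 per arm with education left out, the t-test rejected a true null in 5.2% (r = 0.3) and 4.9% (r = 0.5). The nominal 5% holds.

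**The case against.** An unadjusted t-test in a randomised trial is not an error. Randomisation covers imbalance on average, and collecting a variable creates no duty to model it. The choice of covariates often belongs in an analysis plan, and section 3.4 refers to one that is not shown. All of this is fair, and it sets the weight of the point. It does not remove the point, because section 3.5.1 itself names the test.

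A reader might infer that education is used nowhere at all. The text does not support that: the count-data list is given as examples, so a chi-square comparison of education at baseline may be intended. Such a comparison would not adjust the treatment effect, however.

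A reader might also infer bias or an inflated error rate, or take the 74% to 82% power (r = 0.3 to 0.5) as what adding education would deliver. Step 5 shows no inflation, and those power figures apply only if baseline score stays out of the model. The stronger covariate is the baseline score, which already carries most of a stable literacy effect. If the arms are compared on change scores, which section 3.5.1 leaves unclear, such an effect largely cancels.

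Finally, the voice, video and picture prompts partly offset low literacy. If schooling alters how much a patient gains from the training, that is effect modification, which a main-effect covariate does not address.

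**Conclusion.** The point holds as a minor improvement in precision. The planned comparison is valid on average but discards information the trial already collects. The main loss is the baseline score (51% to 81% of variance at ρ = 0.7 to 0.9); education is secondary. Against the plan as written, education alone is worth 4% to 25% of variance (r = 0.2 to 0.5). With baseline score in the model it is worth about 0.2% to 6%. These figures rest on assumed correlations, and on education being equally related to the score before and after treatment. The documents cannot narrow them, and they do not support a claim of bias.

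**What to change.** In section 3.5.1, replace the between-arm t-test for each ABC and CADL score with a linear model (ANCOVA) of the 2-week score on treatment arm and the corresponding baseline score. Include education, in the form recorded at baseline, as an additional prespecified covariate. Report the adjusted mean difference with its 95% CI. Name education among the baseline characteristics, so that its tabulation does not depend on how the open list is read, and bring the synopsis entry on analysis into line.

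The cost is a sentence or two of text and a standard SPSS procedure. No new data or patients are needed. Education takes one degree of freedom if entered as years, or two if entered as three levels; the baseline score takes one more.
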